### Statistical analysis

Statistical analysis will be performed using SPSS software version 26.0. Measurement data will be presented as means and standard deviations (SD) or medians and interquartile ranges (IQR), as appropriate. Counting data will be expressed as percentages.

Efficacy evaluation will adhere to the intention-to-treat (ITT) principle, including all patients who have received at least one treatment. For the primary outcome (1-hour pad test) and secondary outcomes (72-hour bladder diary, ICIQ-SF scores, I-QOL scores, pelvic floor muscle strength test results, and patient self-evaluation of efficacy), a mixed-effects model will be employed to account for the characteristics of repeated measures data. The model will include group, time points, and their interaction as fixed effects, with participants treated as random effects. Baseline values will be incorporated as covariates.

Missing data will be handled using multiple imputation. Five datasets will be generated based on age, sex, body mass index (BMI), baseline characteristics, and outcome values at other time points for analysis. Two sensitivity analyses will be performed for the primary outcome (1-hour pad test): (1) an analysis of the dataset without imputation to assess potential bias introduced by imputation and (2) an analysis of the per-protocol (PP) set to evaluate the impact of adherence. The PP set is defined as participants who completed at least 80% of the planned treatments without significant protocol violations (i.e., at least five treatments in both the acupuncture and sham acupuncture groups).

Safety analysis will include all participants who received at least one treatment. AE rates will be described using counts and percentages. Between-group comparisons will be conducted using the chi-square test when the expected frequency requirements are met; otherwise, Fisher’s exact test will be used. All statistical analyses will be two-tailed, with a significance level of *P *< 0.05 considered statistically significant.

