#### Shedding criteria.

Subjects who, despite providing informed consent form and passing the screening process to obtain a randomization number, are unable to complete the treatment regimen and observation period specified in the study protocol are considered shedding cases.

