#### Management of shedding cases.

When a subject is shed, efforts should be made to contact them via home visits, scheduled follow-ups, telephone calls, or letters to determine the reasons for shedding. Relevant information should be recorded, including the date of the last acupuncture session and the evaluation items completed up to that point. All data pertaining to shedding cases should be carefully preserved, both for archival purposes and for inclusion in intention-to-treat (ITT) statistical analysis.

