#### Termination criteria.

(1)At least one urologist or gynecologist must participate in this study. If a patient experiences severe adverse reactions that, in the physician’s judgment, necessitate the termination of their participation in the clinical trial, the case should be withdrawn.(2)If the patient develops other conditions that interfere with trial observations and, in the physician’s judgment, the clinical trial should be terminated, the case will be treated as invalid.(3)If a subject decides during the clinical trial that they no longer wish to participate and requests to withdraw from the study, their request should be respected, and they should be allowed to exit the trial.

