### Allocation

This study will adopt a single-center randomized controlled trial design, randomly allocating 72 eligible patients into the acupuncture group or sham acupuncture group in a 1:1 ratio (36 patients in each group). A completely random digital sequence will be generated by third-party personnel using computer software, without setting any blocking or stratification factors, to ensure a fully randomized allocation process. After obtaining the patient’s informed consent form (**S2 File**), sequentially numbered, opaque, sealed, tamper-resistant, and water-resistant envelopes made of polypropylene (PP) will be utilized. The exterior of the envelopes will be labeled with only the random number and unsealing instructions, while group assignments will be concealed inside the envelopes to ensure allocation concealment. Recruitment personnel will screen and enroll patients who meet the inclusion criteria and distribute the envelopes in order. Before the intervention, the acupuncturist will open the envelope on-site to determine group assignment and administer the corresponding treatment.

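### The efficacy set labelled ITT is a modified ITT set, it contradicts the shedding rule for women randomised but never treated, and the status of invalid cases in the analysis is left open

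*Protocol article*

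**What the plan says.** Four places in the protocol article bear on who is analysed for efficacy.

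- **Statistical analysis**, efficacy: "Efficacy evaluation will adhere to the intention-to-treat (ITT) principle, including all patients who have received at least one treatment". The safety set in the same section has the same entry condition: "Safety analysis will include all participants who received at least one treatment".
- **Shedding criteria**: a shedding case is a consenting subject who, after "passing the screening process to obtain a randomization number, are unable to complete the treatment regimen and observation period specified in the study protocol". No minimum number of treatments is required.
- **Management of shedding cases**: all data on these subjects are to be preserved, "both for archival purposes and for inclusion in intention-to-treat (ITT) statistical analysis".
- **Termination criteria**, item (2): if a patient develops another condition that interferes with observation and, "in the physician’s judgment, the clinical trial should be terminated, the case will be treated as invalid". Items (1) and (3) speak instead of withdrawing the case and of letting the patient leave.

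On timing, the Allocation section says: "Before the intervention, the acupuncturist will open the envelope on-site to determine group assignment". The Blinding section says that participants, outcome assessors and analysts are blinded and that acupuncturists are not.

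**The concern.** The intention-to-treat principle protects the comparison because membership of the set is fixed by randomisation and by nothing that happens later. A condition of at least one treatment makes membership depend on a later event. Such a restriction is often harmless, but it has to be named and justified, and here it carries the ITT label.

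The restriction also conflicts with the shedding rule. When the data are prepared, somebody will have to choose between two written rules for the primary analysis population. If that choice is made late, it is no longer prespecified.

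The first treatment comes after an unblinded person has learned the allocation, so an exclusion between opening the envelope and the first needle could in principle depend on arm. The word invalid raises a similar question, since it is applied after randomisation, on a physician's judgment, because of a condition that arose during the trial.

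Neither planned sensitivity analysis (data without imputation, and the per-protocol set) would bring an excluded randomised woman back, so the plan has no check on the restriction.

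**Working it through.** **Step 1. The plan's own number.** The Sample size section starts from 30 per group and allows for 20% dropout. 30 × 1.20 = 36 per group, and 2 × 36 = 72, as stated. (Dividing by 0.80 gives 37.5, so 38 per group. That is a separate matter and has no bearing here.) An all-randomised set therefore has 72 members.

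**Step 2. The rules side by side.**

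| Randomised woman who… | Shedding rules | Statistical analysis section | Result |
|---|---|---|---|
| completes treatment and follow-up | not a shedding case | in | no conflict |
| has one or more treatments, then drops out | kept for ITT | in | no conflict |
| is never treated | kept for ITT | out | direct contradiction |
| has one or more treatments, then is stopped under Termination criterion (2) | kept for ITT, since she did not complete | in | retained, but called invalid with no meaning given for analysis |
| is stopped under criterion (2) before any treatment | kept for ITT | out | contradiction, and called invalid |

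The contradiction created by the one-treatment condition is thus confined to women with zero treatments. Anyone treated once is kept under both rules.

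**Step 3. How many women this could be.** Let k be the number randomised and never treated. The set in the Statistical analysis section has 72 − k members. The documents give no k, so the untreated shares below are assumptions (k = 72 × share, rounded).

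| Assumed share never treated | k | Set size |
|---|---|---|
| 0% | 0 | 72 |
| 2% | 1 | 71 |
| 5% | 4 | 68 |
| 10% | 7 | 65 |
| 20% | 14 | 58 |

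The upper rows are the more plausible ones. The envelope is opened on site immediately before treatment, which leaves little time between learning the allocation and the first needle.

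**Step 4. What cannot be calculated.** The number of cases that will be called invalid, their arm and their outcomes are not in the documents. No bias in the pad-test difference can be derived.

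**The case against.** The strongest reply is that this is a labelling problem that may affect nobody. A woman who leaves while her envelope is sealed leaves with her allocation concealed. After it is opened she is still blinded, so her own decision to leave cannot follow from knowing her arm. Only the short interval between opening and first needling is exposed, and only through the acupuncturist. The trial is also a pilot whose primary objective is feasibility, and its Discussion concedes that the sample may not support definitive conclusions. All of this stands, and it is why the point is kept small. It does not remove the contradiction, because the Introduction also promises evidence of an effect beyond placebo, and that rests on the efficacy set.

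Three stronger readings are tempting, and the documents do not support them.

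- *The unblinded acupuncturist decides who is needled.* The Allocation section says only that the acupuncturist opens the envelope and gives the matching treatment. It describes no discretion to withhold treatment.
- *Invalid cases are removed from the analysis.* No section says so. The contrast with the wording of items (1) and (3) hints at a different consequence, but a woman stopped under item (2) meets the definition of a shedding case, and on that reading her data are already kept. The fair conclusion is ambiguity.
- *The estimate could be distorted by a tenth to a fifth.* Suppose 3 of 36 are excluded, all in one arm, with outcomes 0.5 to 1.0 SD worse. Then 3/36 × 0.5 = 0.042 SD and 3/36 × 1.0 = 0.083 SD, or 10% to 21% of an effect of 0.4 SD. The three exclusions, the gap and the 0.4 SD are all invented; the documents give none of them. Even so, the shift would be small beside a standard error of about √(2/36) = 0.24 SD.

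Nor would widening the set undo a bias of that kind in full. Women with no outcome after baseline would be imputed largely from women who were retained, so an unobserved deficit would mostly not reappear.

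Finally, one could say that analysis sets belong in the statistical analysis plan. That would answer an omission. Here the article states the rule, and states it in two incompatible ways.

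**Conclusion.** The point holds in a limited form. The primary efficacy set is a modified ITT set under an ITT label. It contradicts the shedding rules for women randomised and never treated, and for no one else. The effect of criterion (2) on the analysis is undefined and has to be reconciled with the shedding rules.

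The number affected is k out of 72, unknown and possibly zero. An exclusion that depends on arm is possible in principle because the allocation is known to an unblinded person before the first treatment, but no size can be put on it and none is claimed. The conclusion rests on the wording alone and on no assumed effect or dropout pattern. Severity: should be fixed.

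**What to change.** 1. Define the primary efficacy set as all randomised participants, analysed in the group to which they were allocated, whatever treatment they received. Handle missing outcomes by the planned mixed model or multiple imputation. For a woman with no outcome after baseline, imputation is what keeps her in the analysis, because the mixed model alone has nothing from her to use.
2. In the Termination criteria, state that the data of a case stopped under item (2) are kept and that the case stays in this set, so that the item agrees with the shedding rules. The clinical grounds for stopping do not change.
3. Keep the condition of at least one treatment for the safety set. If an efficacy analysis on that set is wanted, label it modified ITT and list it as a sensitivity analysis.
4. Settle the wording before the efficacy analysis begins, so that the choice between the present rules cannot follow the results.

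The cost is a change of wording in the protocol and the analysis plan, and a few more imputed records. Recruitment, visits and sample size are unaffected.

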**Design and methods:**

This is a randomized controlled trial. Seventy-two PSUI patients between 42 days and 1 year postpartum will be randomly assigned in a 1:1 ratio to either the acupuncture group (n = 36) or the sham acupuncture group (n = 36). Both groups will receive acupuncture treatments three times per week for two weeks. Both groups will receive identical education regarding pelvic floor muscle training. The primary outcomes are changes in urine leakage volume measured by 1-hour pad test at week 2 of treatment and week 6 of follow-up compared to baseline (week -1), and the proportion of patients achieving at least 50% reduction in urine leakage volume at week 2 compared to baseline. Secondary outcomes include 72-hour bladder diary, The International Consultation on Incontinence Questionnaire-Short Form (ICIQ-SF), Incontinence Quality of Life questionnaire (I-QOL), and pelvic floor muscle strength assessment.

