### Sample size

This study is a pilot trial, and for acupuncture clinical research, a sample size of 30 cases per group in pilot trials is suitable for parameter estimation [17], with a 20% dropout rate taken into consideration. Therefore, this study will enroll 36 subjects per group, for a total of 72 subjects.

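### As written, the pad-test model is most naturally fitted with one variance for weeks 2 and 6; a visit-specific covariance would protect the standard errors at both visits

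*Protocol article*

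**What the plan says.** The Statistical analysis section of the protocol article states that "a mixed-effects model will be employed to account for the characteristics of repeated measures data". It then sets out the terms: "The model will include group, time points, and their interaction as fixed effects, with participants treated as random effects". It adds: "Baseline values will be incorporated as covariates". No residual covariance structure is named. The section neither says that the participant effect is the sole within-woman term nor states that variances are equal across visits. Tests are two-sided at 5%.

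The time points that matter are in the Abstract, under Design and methods: "The primary outcomes are changes in urine leakage volume measured by 1-hour pad test at week 2 of treatment and week 6 of follow-up", each compared with baseline. The Introduction makes feasibility the primary objective. As the secondary objective it lists the mean between-group pad-test difference, the SD and Cohen's d, as parameters for sizing the next trial.

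**The concern.** An analyst who follows the sentence literally would enter participant as a random intercept and leave one residual variance. That is compound symmetry: every post-baseline visit has the same variance, and the same standard error serves the group difference at week 2 and at week 6.

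The pad test makes equal variance doubtful. It is a non-negative weight, restricted at entry to more than 1 g and less than 50 g, and such weights are usually skewed, with spread that moves with the mean. All women are advised to train the pelvic floor daily from baseline, and the Introduction says that training needs at least three months for full benefit. Leakage could therefore still be changing between weeks 2 and 6 in both arms, and its spread with it.

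At stake are the standard errors, confidence intervals and p-values of the two visit-specific differences that the Abstract calls primary. The Introduction also wants these differences and SDs for planning, and a single variance presupposes part of what the pilot is meant to estimate.

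**Working it through.** **Inputs from the article.** Two-sided 5% level; weeks 2 and 6; baseline as covariate; 36 per arm. The sample size is the only design figure: 30 × 1.20 = 36 reproduces it. It does not depend on the variance model and is not at issue here.

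**Inputs assumed.** The article gives no post-baseline SD, no between-visit correlation and no expected course of leakage. The baseline-adjusted SD ratio, week 2 to week 6, is varied from 1.0 to 2.0.

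**Formula.** Let v2 and v6 be the variances at the two visits given baseline. With equal numbers at both visits, the random-intercept model uses the pooled value (v2 + v6)/2 at each. At visit t:

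- standard error used ÷ true standard error = √[((v2 + v6)/2) / v_t]
- actual type I error = 2 × [1 − Φ(1.96 × that ratio)]

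**Worked case, SD ratio 1.25.** v2 = 1.5625, v6 = 1, pooled = 1.281. At week 2, √(1.281/1.5625) = 0.906, so the critical value is in effect 1.775 and the error is 7.6%. At week 6, √1.281 = 1.132, in effect 2.219, and the error is 2.7%.

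| SD ratio | Pooled variance (v6 = 1) | SE used ÷ true SE, wk 2 / wk 6 | Type I error, wk 2 / wk 6 | Simulated |
|---|---|---|---|---|
| 1.0 | 1.000 | 1.00 / 1.00 | 5.0% / 5.0% | 5.3% / 4.9% |
| 1.1 | 1.105 | 0.96 / 1.05 | 6.1% / 3.9% | not run |
| 1.25 | 1.281 | 0.91 / 1.13 | 7.6% / 2.7% | 7.7% / 2.5% |
| 1.5 | 1.625 | 0.85 / 1.27 | 9.6% / 1.3% | 9.2% / 1.5% |
| 2.0 | 2.500 | 0.79 / 1.58 | 12.1% / 0.2% | 11.6% / 0.3% |

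The simulation used 36 per arm, no treatment effect, complete normal data, two post-baseline visits and 6,000 runs per scenario. The Monte Carlo standard error at 5% is √(0.05 × 0.95/6000) = 0.3 percentage points. With a separate variance at each visit, type I error was 4.7% to 5.7% in every scenario. The group-by-time test stayed at 4.6% to 5.4%, because with two visits its variance comes directly from the within-woman differences.

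**Direction.** Because baseline is a covariate, what counts is v_t = s_t² × (1 − r_t²), where s_t is the raw SD and r_t the correlation with baseline.

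- Raw SD ratio 1.44, correlations 0.8 (week 2) and 0.5 (week 6): 2.074 × 0.36 = 0.746 against 0.75. The variances match, and simulated error is 4.8%/4.9%.
- Raw SD ratio 1.25, correlations 0.8 and 0.4: 1.5625 × 0.36 = 0.5625 against 0.84. The direction reverses, and simulated error is 3.1%/7.7%.
- Equal raw SDs, correlations 0.8 and 0.4: 0.36 against 0.84. Error is 1.5%/8.9%, so equal raw spread alone gives no assurance.
- Raw SD ratio 1.6 (falls of 20% and 50% with proportional spread, 0.8/0.5), correlations 0.7 and 0.5: 2.56 × 0.51 = 1.306 against 0.75. The closed form gives about 8.2%/2.2%.

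**The case against.** The strongest reply is that nothing in the article is wrong. A participant random effect does not exclude a visit-specific residual structure, and the choice of residual covariance and its convergence fallback commonly sits in an analysis plan, which is not shown here. A reader might infer that the plan fixes a random intercept as the sole structure and so forces equal variances. The text does not support that: it is silent on the residual structure and does not say that the participant effect is the only term. What remains is that the one structure it does name leads most directly to the equal-variance model.

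A reader might also infer that the p-values go wrong whenever leakage keeps falling. That does not follow. A falling mean changes nothing by itself. The trigger is unequal variance given baseline, and a weaker baseline correlation at week 6 can cancel or reverse the effect of a shrinking raw SD. This part of the objection stands in full.

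Two further points also stand. In balanced data the covariance choice does not bias the estimated mean differences or disturb the group-by-time test. And the trial is a pilot with a feasibility objective, sized for parameter estimation, so no decision in the article depends on a visit-specific p-value crossing 0.05.

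**Conclusion.** The point holds conditionally. Fitted in its most natural form, the stated model carries one variance for weeks 2 and 6. If spread given baseline differs between the visits, inference at each visit is distorted in opposite directions: about 7.6%/2.7% at an SD ratio of 1.25 and 9.6%/1.3% at 1.5, with no distortion at 1.0. These sizes rest entirely on assumed SD ratios, two post-baseline visits and complete data. Which visit would be affected in which direction cannot be read from the article, so it would be too strong to say that the week-2 or week-6 p-value is wrong. The practical consequence is modest in a feasibility pilot, but it falls on the precision of the differences named as primary and intended for planning. It is a cheap improvement, not the correction of an error.

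**What to change.** Keep group, time, their interaction and the baseline covariate. In place of the participant random intercept, model the post-baseline visits with an unstructured residual covariance (the REPEATED specification in SPSS MIXED). Name heterogeneous compound symmetry as the fallback if the model does not converge. Report the week-2 and week-6 group differences, each with its own standard error and confidence interval. Fix this before unblinding.

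The cost is one sentence of analysis wording and no new data. With two visits the unstructured form has three covariance parameters (two variances and one covariance) against two for the random intercept. With three visits it has six against two, and the fallback has four. With only two visits, the fallback and the unstructured form are the same model. There is a slight loss of degrees of freedom if the variances turn out equal.

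### The mixed model gives the baseline value one slope for all visits; adding a baseline-by-time term would be a small, nearly free improvement

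*Protocol article*

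**What the plan says.** The Statistical analysis section of the protocol article describes one model for the primary and the repeated secondary outcomes: "The model will include group, time points, and their interaction as fixed effects, with participants treated as random effects". The next sentence is "Baseline values will be incorporated as covariates". Group by time is the only interaction named. A baseline-by-time term is neither included nor ruled out.

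The abstract (Design and methods) gives the continuous primary outcome as "changes in urine leakage volume measured by 1-hour pad test at week 2 of treatment and week 6 of follow-up compared to baseline", so two visit-specific group contrasts are of primary interest. Missing values are multiply imputed, so the main analysis runs on completed data. Allocation is 1:1, "without setting any blocking or stratification factors". The Introduction lists the pad-test SD among the quantities that this pilot is meant to estimate. No correlation between baseline and later visits is given.

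**The concern.** A plain baseline covariate forces the same regression slope on baseline at week 2 and at week 6. Pad weight is measured in grams and cannot fall below zero, so its spread, and with it the slope on baseline, may change as average leakage changes. If the two slopes differ, the shared one lies between them and is wrong at both visits: too small at one and too large at the other. Part of a chance baseline difference between the arms then stays in one visit's estimate and is over-corrected in the other's. The pair of estimates can look like a treatment effect that changes over time.

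The Introduction says that the between-group difference and Cohen's d will feed the next trial's sample size. The Discussion says that the results will inform whether treatment and follow-up should be longer. Both uses gain from visit estimates that are as clean as the data allow.

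**Working it through.** **Inputs from the protocol.** 36 women per arm ("this study will enroll 36 subjects per group, for a total of 72 subjects"; 30 × 1.2 = 36), visits at weeks 2 and 6, one baseline slope, completed data. Everything else below is assumed.

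**Algebra.** Scale the baseline to SD 1. Let b2 and b6 be the true slopes of the week-2 and week-6 values on baseline, and SDt the outcome SD at visit t. With both visits complete and a random participant intercept:

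- The shared slope is b = (b2 + b6)/2.
- With the visit's own slope, the adjusted variance at visit t is SDt² − bt². With the shared slope it is SDt² + b² − 2·b·bt, which is larger by (b − bt)².
- For a baseline difference Δ between the arms, the uncorrected remainder is (b2 − b)Δ at week 2 and (b6 − b)Δ at week 6. These are equal in size and opposite in sign.
- In the week-6 minus week-2 difference, b cancels. Its variance is var(Y6 − Y2), against var(Y6 − Y2) − (b6 − b2)² with visit-specific slopes. In fitted mixed models, the group-by-time estimate with the shared slope equalled that of a model with no baseline term, to about 2e-15.

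**Worked case.** Equal SDs of 1, correlations with baseline 0.7 (week 2) and 0.5 (week 6), correlation between the two visits 0.7; b = 0.6.

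- Week 2: 1 + 0.36 − 0.84 = 0.52 against 1 − 0.49 = 0.51. SE ratio √(0.52/0.51) = 1.010.
- Week 6: 1 + 0.36 − 0.60 = 0.76 against 1 − 0.25 = 0.75. SE ratio √(0.76/0.75) = 1.007.
- Group by time: 0.60 against 0.60 − 0.04 = 0.56. SE ratio √(0.60/0.56) = 1.035.
- A one-SE baseline imbalance is √(2/36) = 0.236 SD. It leaves 0.1 × 0.236 = 0.024 SD at each visit, with opposite signs. Dividing by the SE of each estimate, this is 0.1/√0.52 = 0.14 SE at week 2 and 0.1/√0.76 = 0.11 SE at week 6.

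**Other assumed inputs** (SE loss from the shared slope):

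| SD wk 2 / wk 6 | r with baseline | b2, b6 | Week 2 | Week 6 | Group × time |
|---|---|---|---|---|---|
| 1 / 1 | 0.6 / 0.6 | 0.60, 0.60 | 0% | 0% | 0% |
| 1 / 1 | 0.7 / 0.6 | 0.70, 0.60 | 0.2% | 0.2% | 0.8% |
| 1 / 1 | 0.5 / 0.7 | 0.50, 0.70 | 0.7% | 1.0% | 3.5% |
| 0.8 / 0.5 | 0.7 / 0.6 | 0.56, 0.30 | 2.6% | 5.2% | 12.1% |
| 0.5 / 0.8 | 0.7 / 0.6 | 0.35, 0.48 | 1.6% | 0.5% | 2.7% |

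In the third and fifth rows the steeper slope is at week 6, so the direction of the mis-adjustment reverses.

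**Simulation on the gram scale.** Assumed lognormal baseline with mean 11 g and SD 9 g, cut to the entry range of 1–50 g; later leakage proportional to baseline; log-scale noise SD 0.35–0.6 between women and the same within women; 36 per arm; no treatment effect; 6,000 trials per setting.

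- 75% then 50% of baseline: SE loss about 1–2% at week 2, 3–5% at week 6 and 5–10% for group by time. A one-SD chance imbalance (about 1.8 g after the cut) leaves +0.10 to +0.20 SE at week 2 and −0.16 to −0.25 SE at week 6.
- 80% then 70%: about 0.5% and 1% at the two visits.
- 50% then 70%: about 1–4% at week 2 and 1–2% at week 6, with the signs of the shifts reversed.
- 60% at both visits: the extra term cost nothing measurable.

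**The case against.** The strongest reply is that one baseline slope is a common and valid choice, that randomisation keeps the estimates unbiased, and that a condensed article may leave the exact form of the covariate to an analysis plan that is not shown. All of this stands. The shared-slope covariate also already secures most of the gain: in the worked case, dropping baseline altogether would raise the SE by 40% at week 2 (1/√0.51) and 15% at week 6 (1/√0.75), against about 1% for sharing the slope. Group by time, where the loss is largest, is not a named endpoint. The trial's primary objective is feasibility, which this choice does not touch.

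What remains is that the section does list its fixed effects, and the list as written gives a single slope.

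Two stronger readings are tempting and not supported:

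- A reader might infer that the model under-adjusts at week 2 and over-adjusts at week 6. That needs a steeper slope at week 2. Continued pelvic floor training in both arms could produce it, but needling stops at week 2 and leakage could partly return. The protocol gives no figures to decide.
- A reader might infer that allocation without blocks or strata makes a baseline imbalance in pad weight likely. Blocking balances arm sizes, not pad weight. Imbalance arises by chance and averages zero; the shifts above are conditional on one having occurred.

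**Conclusion.** This is a minor improvement and not an error in the plan. On the literal wording, baseline has one slope. If the true slopes at weeks 2 and 6 differ, the two primary contrasts keep opposite-signed parts of any chance baseline imbalance and lose a little precision. Under assumed leakage of 75% then 50% of baseline, the SE loss is about 1–2% at week 2 and 3–5% at week 6; it is near nil when the slopes are similar. Neither the size nor the direction can be fixed from the protocol.

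The one result that needs no assumed slopes is that, with completed data and a random participant intercept, the group-by-time contrast gets no baseline adjustment. That contrast is still valid in a randomised trial, but less precise than it could be if the slopes differ. The averaging of the two slopes assumes that weeks 2 and 6 are the only post-baseline visits in the model; with further visits the shared slope averages over all of them.

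**What to change.** In the Statistical analysis section, add baseline value by time point to the listed fixed effects, for the 1-hour pad test and for the other repeated outcomes that have a baseline. State that the group differences at week 2 and week 6 are reported from that model. If an analysis plan already contains the term, bring the article's wording into line with it.

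The cost is one sentence and one extra parameter per additional visit. It needs no new data, visits or patients. When the slopes are in truth equal, the precision lost is not measurable: in the equal-slope simulation with normal data, the SE changed by no more than about 0.6% for any of the three contrasts.
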